## Abstract

**Introduction:**

High adherence to oral anticoagulants is essential for stroke prevention in patients with atrial fibrillation (AF). We developed a smartphone application (app) that pushes alarms for taking medication and measuring blood pressure (BP) and heart rate (HR) at certain times of the day. In addition to drug alarms, the habit of measuring one’s BP and HR may reinforce drug adherence by improving self-awareness of the disease. This pilot study aims to test the feasibility and efficacy of the smartphone app-based intervention for improving drug adherence in patients with AF.

**Methods and analysis:**

A total of 10 university hospitals in Korea will participate in this randomised control trial. Patients with AF, being treated with edoxaban for stroke prevention will be included in this study. Total of 500 patients will be included and the patients will be randomised to the conventional treatment group (250 patients) and the app conditional feedback group (250 patients). Patients in the app conditional feedback group will use the medication reminder app for medication and BP check alarms. The automatic BP machine will be linked to the smartphone via Bluetooth. The measured BP and HR will be updated automatically on the smartphone app. The primary endpoint is edoxaban adherence by pill count measurement at 3 and 6 months of follow-up. Secondary endpoints are clinical composite endpoints including stroke, systemic embolic event, major bleeding requiring hospitalisation or transfusion, or death during the 6 months. As of 24t November 2021, 80 patients were enrolled.

**Ethics and dissemination:**

This study was approved by the Seoul National University Bundang Hospital Institutional Review Board and will be conducted according to the principles of the Declaration of Helsinki. The study results will be published in a reputable journal.

**Trial registration number:**

KCT0004754.

Strengths and limitations of this studyThis randomised control trial investigates the feasibility and efficacy of a smartphone application (app)-based intervention for improving adherence to edoxaban in multiple centres.The patient gets alarm to take medication and measure blood pressure with heart rate using an automated electronic manometer according to the prespecified schedule on smartphone app.The physician can obtain the information regarding the blood pressure and heart rate data and drug adherence by checking the app on the follow-up visit.The sample size was calculated to show the difference in drug adherence, and not for any clinical events.The study results may not be applicable to patients who are not capable of using smartphones.

## Introduction

Stroke prevention with oral anticoagulants is crucial in the management of atrial fibrillation (AF).^1^ The large randomised control trials with AF patients have consistently shown comparable effectiveness and improved safety of non-vitamin K oral anti-coagulants (NOAC) compared with warfarin.^2–6^ Based on these trials, the current global guidelines recommend NOACs over warfarin for stroke prevention in patients with AF.^1 7 8^

In contrast to warfarin, NOACs have predictable effectiveness and minimal drug interactions. Consequently, regular blood tests for the monitoring of anticoagulation effects are not necessary with NOAC therapy. The use of NOACs is increasing worldwide because of these advantages.^9 10^ However, there are some concerns regarding the relatively short half-life on NOACs. When doses are missed, a prothrombotic status might adversely triggered.^11^ Thus, in NOAC therapy, consistent drug adherence is essential to maintain a consistent anticoagulation effect for stroke prevention. Poor drug adherence or failed persistence would increase the risk of stroke, and this may lead to an increase in public healthcare costs.^12^

Even though there are controversies regarding their efficacy, smartphone applications (apps) are currently being recognised as an effective tool for promoting drug adherence.^13–23^ Smartphone apps send notifications or push alarms reminding the patient to take their medication. Moreover, active involvement in measuring their health status—blood pressure (BP) and heart rate (HR) using smartphone app-based feedback system could improve awareness of their underlying condition. This in turn influences their self-care behaviour and increases drug adherence.^24^ The aim of this study protocol is to test whether smartphone app-based intervention that provides push alarms for taking medication and measuring BP and HR, would increase the drug adherence compared with usual care in AF patients requiring oral anticoagulation therapy.

## Methods and analysis

### Study design

The Adhere-App (Self-awareness of Drug Adherence to Edoxaban Using an Automatic App. Feedback System) study is a multicentre, randomised, open-label and group-comparison trial to assess the effect of using a smartphone app to improve drug adherence (figure 1). A total of 10 tertiary university hospitals in Korea will participate in this study. The study participants will be randomised to a smartphone app-conditioned feedback group or a conventional treatment group. Every patient will receive education on AF and the importance of anticoagulation therapy. Additionally, the intervention group will be educated on the use of the smartphone app coupled with BP and HR measurement using an automatic BP measuring machine. Study visits will be performed at baseline, 3 months and 6 months (figure 2). When clinical visits are not possible due to the inevitable situation, the patient’s condition and survey data can be collected by telephone visit. This study was registered in the International Clinical Trials Registry Platform on 20 February 2020. However, initiation was delayed due to COVID-19 pandemic. As of 24November 2021, 80 patients were enrolled.

**Figure 1 F1:**
[figure not shown]
Schematic diagram of expected improvement in NOAC adherence by regular measurement of BP, HR and smartphone feedback in patients with atrial fibrillation. BP, blood pressure; HR, heart rate; NOAC, non-vitamin K oral anti-coagulant.

**Figure 2 F2:**
[figure not shown]
Study design of Adhere-App study. Patients using edoxaban will be randomised to either an application conditioned-feedback group or a conventional therapy group.

### Study participants

Adult patients (≥19 years old) with non-valvular AF requiring oral anticoagulation therapy (CHA_2_DS_2-_VASC score ≥2 points) for stroke prevention will be enrolled. Edoxaban (Lixiana, Daiichi Sankyo, Tokyo, Japan) will be administered to patients at an on-label dosage of 60 mg once daily. The dosage will be reduced to 30 mg once daily in patients who meet any of the following criteria: moderate renal impairment (creatinine clearance 30–50 mL/min), body weight less than or equal to 60 kg, or concomitant use of potent P-glycoprotein inhibitors.

Since smartphone usage is crucial in this study, participants should be able to use smartphone well and be capable of following instructions on how to use the app in Korean language. Patients with severe renal insufficiency (creatinine clearance <15 mL/min) and significant mitral valve disease will be excluded. The detailed inclusion and exclusion criteria for the Adhere-App study are listed in box 1.

Box 1Key inclusion and exclusion criteria for Adhere-App studyInclusion criteriaPatients with atrial fibrillation, treated with edoxaban for stroke preventionAge≥19 years Ÿ Capable of using smartphone applicationCompetency in Korean language.Accepted for the study protocol and willing to participate in the clinical study.Exclusion criteriaCreatinine clearance less than 15 mL/minPatients with dual antiplatelet therapyModerate or severe mitral stenosisHistory of mitral valve replacement or mitral valve repairPrevious history of alcohol or drug abuseNot suitable for the clinical trial enrolment by the judgement of the investigatorHistory of previous enrolment in another clinical trial using an investigational pharmaceutical productPatient unwilling to participate in the clinical study.

At baseline, age, sex, details of comorbidities and laboratory findings will be assessed for all patients. The CHA_2_DS_2_-VASc score for stroke risk prediction is calculated by the summation of all assigned points for each particular medical condition: one point each for age between 65 and 74 years (A), female sex (Sc), hypertension (H), diabetes mellitus (D), congestive heart failure (C) and vascular disease (V, prior myocardial infarction or peripheral artery disease) and two points each for a history of stroke/transient ischaemic attack/thromboembolism (S_2_) or age of ≥75 years (A_2_).^25^

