### Statistical analysis

Categorical variables will be presented as numbers and frequencies, whereas continuous variables will be presented as means±SD. The Student’s t-test and Kruskal-Wallis test will be used to compare continuous variables depending on the presence of normally distributed variables. The χ^2^ test will be used to compare categorical variables. A p<0.05 was considered significant. The analysis would be performed according to the intention-to-treat principle. The standard regimen of edoxaban is once daily. The primary endpoint of edoxaban adherence will be calculated by pill count as shown below.

$$Pillcountadherence(\%)=\;\frac{Numberofpillsdispensed-Numberofpillsremaining}{Numberofdaysbetweendispensingdateandfollowupdate}\times 100$$

Since new drug users might have a lower adherence than continuous users, subgroup analysis will also be performed on the new and continuous users. To evaluate the feasibility and efficacy of the smart phone application, further analysis can be performed according to the frequency of the smart phone application use. The secondary endpoints of adverse events will be compared with the Kaplan-Meier curve analysis. A log rank test will be used to evaluate the significance of the difference between the two groups. Statistical analysis will be performed using IBM SPSS Statistics for Windows V.16.0 (IBM) and R software V.4.0.3.

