### Strengths and limitations

Several limitations of this study should be addressed. The study participants do not represent the general population with AF. All participants should be able to use smartphone apps without difficulties. Thus, the results of the study may not be applicable to patients who are not capable of using smartphones, such as the extreme elderly. Second, the study participants who agree to participate in the study might have a higher interest in their own health. Consequently, higher adherence to drug therapy might be observed than that of the general AF population. Third, the sample size was calculated to show the difference in drug adherence. It is not powered to show any differences in clinical events. Despite these limitations, a major strength is that this study is a multicentre randomised control trial with a relatively large number of participants.

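### The renal criterion for 30 mg edoxaban (creatinine clearance 30–50 mL/min) and the renal exclusion (below 15 mL/min) do not meet: read literally, an eligible patient at 15 to <30 mL/min with no other reduction criterion gets 60 mg

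*Protocol article*

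**What the plan says.** All the relevant statements are in the protocol article, Study participants.

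- **Default dose.** Edoxaban "will be administered to patients at an on-label dosage of 60 mg once daily".
- **Reduction.** "The dosage will be reduced to 30 mg once daily in patients who meet any of the following criteria". The list has three entries: "moderate renal impairment (creatinine clearance 30–50 mL/min), body weight less than or equal to 60 kg", and use of a potent P-glycoprotein inhibitor. The renal entry is a closed range with 30 mL/min as its lower end.
- **Renal exclusion.** "Patients with severe renal insufficiency (creatinine clearance <15 mL/min) and significant mitral valve disease will be excluded". Box 1 repeats the 15 mL/min limit as a separate exclusion criterion.
- **Baseline data.** "At baseline, age, sex, details of comorbidities and laboratory findings will be assessed for all patients".

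No other section of the article gives a dose for creatinine clearance between 15 and 30 mL/min.

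**The concern.** A rule that halves an anticoagulant dose because clearance is reduced should not return to the full dose when clearance is worse. As printed, it does so for one group of eligible patients. The wording also calls 30–50 mL/min moderate and below 15 mL/min severe, so the band between them has neither a category nor a renal dose.

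What is at stake is dosing safety, not the trial's main inference. The secondary composite counts major bleeding and death, no data monitoring committee is planned, and 10 hospitals take part. Most participants appear to be on edoxaban already, since the abstract says "Patients with AF, being treated with edoxaban for stroke prevention will be included in this study". However, the Statistical analysis section also expects new users ("subgroup analysis will also be performed on the new and continuous users"), so for some patients the dose may be chosen close to enrolment. At 24 November 2021, 80 of the planned 500 patients had been enrolled, which left 500 − 80 = 420 still to come.

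**Working it through.** **Inputs** (all from Study participants):
- exclude if creatinine clearance (CrCl) < 15 mL/min
- 30 mg if 30 ≤ CrCl ≤ 50 mL/min, or weight ≤ 60 kg, or a potent P-glycoprotein inhibitor is used
- otherwise 60 mg

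**Step 1. Apply the printed rule** to a patient not on a P-glycoprotein inhibitor, once at 70 kg and once at 60 kg.

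| CrCl (mL/min) | 70 kg | 60 kg |
|---|---|---|
| 14.9 | excluded | excluded |
| 15 | 60 mg | 30 mg |
| 20 | 60 mg | 30 mg |
| 29.9 | 60 mg | 30 mg |
| 30 | 30 mg | 30 mg |
| 40 | 30 mg | 30 mg |
| 50 | 30 mg | 30 mg |
| 50.1 | 60 mg | 30 mg |
| 80 | 60 mg | 30 mg |

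For the 70 kg patient the dose runs 60, 30, 60 mg as clearance rises from 15 mL/min. In the 15 to <30 mL/min band it is 60/30 = 2 times the dose at 30–50 mL/min. The 60 kg column shows that the anomaly disappears once another reduction criterion applies, so it is confined to patients who meet none.

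**Step 2. Test both ways of closing the gap.**
- Reduction criterion 15–50 mL/min: CrCl 15, 20 and 29.9 give 30 mg, and every eligible patient from 15 to 50 mL/min is covered.
- Exclusion below 30 mL/min: CrCl 15, 20 and 29.9 are excluded, and every eligible patient from 30 to 50 mL/min gets 30 mg.

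Either change makes the limits meet. The article alone cannot choose between them, because it does not reproduce the label.

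**Step 3. Check for any effect on the primary analysis.** The adherence formula divides pills taken by days elapsed, and both doses are once daily, so the milligram strength does not enter it (taking each dose as one tablet, as the formula implies). The dose rule is the same in both arms. The stated 234 per group follows from the difference of 5.0, SD of 15.0, two-sided alpha of 0.05 and 95% power: 2 × (1.960 + 1.645)² × 15²/5² = 2 × 12.996 × 9 = 233.9, rounded up to 234. No term depends on the edoxaban dose.

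**The case against.** The best defence is the word on-label. It governs the dosing sentence, so the list can be read as a shortened summary of the label that leaves out 15 to <30 mL/min and does not assign it 60 mg. Edoxaban is also largely background therapy, because the trial randomises to the app or usual care. Sites would be expected to work from the full protocol and the label, not from a journal article, and Box 1 lets an investigator exclude an unsuitable patient.

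Most of this stands, and it makes actual misdosing unlikely. It does not repair the text. The article does not reproduce the label, on-label is attached to 60 mg, and a closed range is then printed that conflicts with a stated eligibility limit. Condensing a protocol explains an omission but not two printed limits that fail to meet. Investigator discretion is not a dose rule.

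Three stronger readings are tempting, and the documents support none of them.
- A reader might infer that 30 mL/min is the wrong number. The article shows only that the two limits do not meet; the exclusion limit could be the one at fault.
- A reader might infer that patients were given the wrong dose. Nothing in the article shows this.
- A reader might take the width of the band, 15 of the 35 mL/min between 15 and 50, as a measure of impact. It is a share of a clearance scale and says nothing about the number of patients.

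**Conclusion.** The inconsistency is real and can be verified from one section of the article. Under the printed rule, an eligible patient at 15 to <30 mL/min, over 60 kg and not on a potent P-glycoprotein inhibitor, gets 60 mg, twice the dose at 30–50 mL/min. This rests on reading the printed criteria literally, without the label.

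It is a minor dosing-safety correction. The number of patients in the band is not given and no estimate is made; it is probably small. Confidence is high that the gap exists in print, but does not extend to which limit is wrong or to any actual misdosing. The adherence endpoint, sample size and analysis are unaffected. For clinical events the article already says of its sample size, "It is not powered to show any differences in clinical events".

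**What to change.** Make the two limits meet, and confirm the wording against the label that the text says it follows.

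- **Preferred wording.** Change the renal reduction criterion to creatinine clearance 15–50 mL/min. The 15 mL/min eligibility limit is stated twice, so this is the least disruptive change and leaves eligibility alone.
- **If the label does not support 30 mg at 15 to <30 mL/min.** Raise the exclusion to below 30 mL/min, in both the text and Box 1.
- **Patients already enrolled.** Use the baseline laboratory data to find anyone at 15 to <30 mL/min and confirm the current edoxaban dose. The existing exclusion already requires clearance to be known, so no new test is needed.

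The cost of the preferred route is a one-line amendment and a record check limited to that band, among the 80 patients enrolled at 24 November 2021 and any since. The alternative also narrows eligibility. Neither changes the endpoint, sample size or analysis.

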### Patient and public involvement

Patients or the public will not be involved in the design, reporting, or dissemination of our research.

### Patient recruitment and randomisation

Potential participants will be any patients visiting the clinic for AF management. After a comprehensive interview, written informed consent will be obtained from all eligible participants. Eligible participants will be asked to complete a baseline survey covering demographics and cardiovascular comorbidities. The eligible participants will then be randomly assigned to either the intervention group or the conventional treatment group in a 1:1 ratio using a web-based central randomisation service (http://matrixmdr.com/). Allocation concealment would be ensured, as the service would not release the randomisation results until the patient has been enrolled into the trial. Due to the nature of the intervention, it is not possible to blind participants to group allocation. All participants will be informed that the information on edoxaban adherence will be collected for analysis.

### Intervention (Smartphone app-conditioned feedback)

Study participants in the intervention group will instal the study app provided by clinical research coordinators on their own smartphone. Since the app is not an open application to the public, the control group can’t access to application. The operating system and sample display of the smartphone app are summarised in figure 3. The participants can set the alarm for taking edoxaban at a certain time of the day. The research coordinator or the physician will set the alarm initially. Patient’s exercise information, including interval, exercise type and duration, will be submitted on the first visit. When the alarm sounds at the prespecified time, the patient will be asked to take the drug (edoxaban) and measure their BP and HR using an automated electronic manometer (UA-651BLE Bluetooth Blood Pressure monitor, A&D Medical, Sydney, Australia). The measured BP and HR data will be automatically transmitted to the smartphone via Bluetooth, as shown in online supplemental figures 1–4. To evaluate awareness of disease status, the app will ask whether the measured BP result is optimal, and the patient is required to respond to the question. The app will also check whether the patient took the medication. If the patient does not affirm taking the medication, the app will send an alert message to ensure that the patient takes the medication. The data regarding the time of edoxaban intake, BP and HR will be automatically updated and stored daily. Finally, the physician can obtain feedback on BP and HR measurement data and drug adherence by checking the app on the follow-up visit. The aforementioned functionalities will be provided by the smartphone app, while a standalone web application has been developed for physicians to monitor associated patients’ BP, physical activity and medication adherence trends. The design, development and utilisation detail of the patient-oriented smartphone app and physician-oriented web app are described in online supplemental material 1.

10.1136/bmjopen-2021-048777.supp1Supplementary data

10.1136/bmjopen-2021-048777.supp2Supplementary data

10.1136/bmjopen-2021-048777.supp3Supplementary data

10.1136/bmjopen-2021-048777.supp4Supplementary data

10.1136/bmjopen-2021-048777.supp5Supplementary data

**Figure 3 F3:**
[figure not shown]
Operating system and sample display of the smartphone app. When the patient measures BP, the data are automatically transferred to the app via Bluetooth system. (A) title page; (B) menu bar indicating BP measurement, log-out, alarm setting, manual BP input and password setting; (C) alarm setting page for medication; (D) exercise information including interval, exercise type and duration; (E) alarm page to check whether the patient has taken medication; (F) bp manual input page; (G) page displaying measured BP and HR result; (H) feed-back question to check whether the patient has achieved optimal target BP. BP, blood pressure; HR, heart rate.

### Control (conventional treatment)

In the control group, only usual guideline-recommended treatments, including education on the disease and the importance of taking medications by physicians at every routine visit will be covered. No other specific interventions will be made. Patients will be followed up in clinics according to the study protocol (3 months and 6 months) and be provided usual care for AF.

### Study endpoints and follow-up

The primary endpoint is edoxaban adherence by pill count measurement at second (3 months) and third (6 months) visits. All patients will be asked to bring their remaining pills at each clinical visit. Secondary endpoints are clinical composite endpoints, including stroke, systemic embolic event, major bleeding requiring hospitalisation or transfusion, or death during the 6 months of follow-up by electronic medical records. The primary and secondary endpoints will be compared between smartphone app-conditioned feedback group and control group. An additional predefined observational parameter is symptom change related to BP (both systolic and diastolic) and HR. Clinical research coordinators will ask symptoms as an open question and each investigator will determine whether the symptom is related with BP and HR change. The study participants would be followed up relatively short period (6 months) and the protocol of current research carries only minimal risk. Thus, data monitoring committee and interim analysis plan would not be established.

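### Electronic medical records are the sole source named for the secondary clinical events, and the 3- and 6-month contacts are not said to be used to ask about them, so events treated elsewhere can be missed

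*Protocol article*

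**What the plan says.** In Study endpoints and follow-up, the Protocol article defines the secondary composite as "stroke, systemic embolic event, major bleeding requiring hospitalisation or transfusion", "or death during the 6 months of follow-up by electronic medical records". No second source is named for any component.

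The same section does describe one question put to patients: "Clinical research coordinators will ask symptoms as an open question". It serves a separate observational parameter, symptoms related to blood pressure and heart rate, and not the composite.

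Study design sets the contacts: "Study visits will be performed at baseline, 3 months and 6 months". If a clinic visit is impossible, "the patient’s condition and survey data can be collected by telephone visit". The section on the control arm repeats the 3- and 6-month follow-up, so both arms have it. The sites are ten tertiary university hospitals.

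In Statistical analysis, "The secondary endpoints of adverse events will be compared with the Kaplan-Meier curve analysis", with a log-rank test between arms. The article states no censoring rule.

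**The concern.** The components of this composite are acute. A stroke or a bleed needing transfusion may be treated at whichever hospital is nearest, and a death may occur outside any hospital. The article describes no link to other hospitals or to a death register. A site's record can then stay silent, most of all for a patient who dies or is admitted elsewhere and does not come back.

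In a time-to-event analysis, an event that is not recorded counts as event-free follow-up until whatever censoring date applies. The estimated event rates are then too low. The Discussion says the trial will also assess the effect of the app on adverse clinical events, so these rates will be reported and read. The contacts that could close the gap are already scheduled.

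**Working it through.** **Passages side by side.**

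1. Source of events: the site's electronic medical record (Study endpoints and follow-up).
2. Patient contact: 3 and 6 months in both arms, with telephone as the fallback (Study design; Control).
3. What is asked at contact: symptoms, for the blood pressure and heart rate parameter. The telephone visit collects the patient's condition and survey data. Neither text mentions stroke, embolism, bleeding, hospital stays or death.
4. Analysis: Kaplan-Meier and log-rank, with no censoring rule stated.

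Items 1 and 3 together leave no described route by which an event treated elsewhere reaches the data. Item 4 means that an event which does not reach the data adds event-free time.

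**Size (illustration only).** The plan has no figure on this point to reproduce. Its sample-size figures concern pill-count adherence. The event risks, capture fractions and hazard ratio below are assumptions.

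- Counted events = 500 × p × c, where p is the true 6-month risk and c is the fraction of events that the records capture.
- Observed risk is about p × c.
- Log-rank power (Schoenfeld, 1:1, two-sided 0.05) = Φ(√D / 2 × |ln HR| − 1.96), with D counted events and an assumed hazard ratio of 0.5.

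| True risk p | True events | Counted at c = 0.9 / 0.7 | Observed risk at c = 0.9 / 0.7 | Power, full capture | Power at c = 0.9 / 0.7 |
|---|---|---|---|---|---|
| 1% | 5 | 4.5 / 3.5 | 0.9% / 0.7% | 12% | 11% / 9.5% |
| 2% | 10 | 9 / 7 | 1.8% / 1.4% | 19% | 18% / 15% |
| 4% | 20 | 18 / 14 | 3.6% / 2.8% | 34% | 31% / 25% |

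Worked line: p = 4% and c = 0.7 give D = 500 × 0.04 × 0.7 = 14. Then √14 / 2 × 0.693 − 1.96 = −0.66, and Φ(−0.66) is about 0.25.

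Events needed for 80% power at a hazard ratio of 0.5: 4 × (1.96 + 0.84)² / (ln 0.5)² = 66 after rounding up. The comparison is underpowered with or without full capture, so the damage is to the reported rates rather than to a usable test.

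**Between arms.** If both arms lose the same fraction and there is no true effect, the risk ratio stays at c/c = 1.0.

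**The case against.** The strongest reply is that the article does not make records the exclusive source. Patients in both arms are seen twice, the telephone visit collects their condition, and a physician who hears of an outside event may well enter it in the record. The article says neither that this happens nor that it does not. Case report form questions, retrieval of outside records and censoring rules also commonly sit in a full protocol or analysis plan that is not shown. All of this stands, and it means that loss of events is a risk and not an established fact. It does not remove the point, because the article states a method for finding events and a better one is available from contacts already planned.

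A reader might go further in three ways that the article does not support.

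- **That unrecorded patients are assumed event-free to 6 months.** No such rule is written; the censoring date is simply not given.
- **That capture differs by arm, because "a standalone web application has been developed for physicians to monitor associated patients’ BP, physical activity and medication adherence trends".** Unequal capture would distort the ratio: 0.90 / 0.80 = 1.13, or 0.90 / 0.70 = 1.29, against the app with no true effect. But the Intervention section mainly describes the physician checking the app at the follow-up visit, which both arms have. It describes no alert to the physician and no extra contact. Nor would blood pressure or adherence trends by themselves reveal a transfusion at another hospital. This is a possibility only.
- **That biased rates will mislead the full-scale study.** The article lists sample size, recruitment rate, study period and data management among what the pilot informs. It does not name event rates or state the later study's endpoint.

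Finally, the endpoint is secondary, and Strengths and limitations says the trial is not powered for clinical events. That limits the weight of the point. It concerns precision, however, and does not correct rates that are too low.

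**Conclusion.** The point holds as a low-severity, inexpensive improvement. Electronic medical records are the sole source the article names for the composite, and the scheduled contacts are not said to be used to ask about events. Events managed outside the sites can be missed and would then be analysed as event-free time, so event rates can be understated.

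The size cannot be fixed from the article. Under the assumed capture of 70% to 90%, rates would be understated by 10% to 30% in relative terms, or 1 to 3 events where 10 truly occur. This rests on some events being treated elsewhere and not finding their way into the site record. Bias between arms is not shown, and the primary adherence endpoint is untouched.

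**What to change.** Amend Study endpoints and follow-up so that events are ascertained from the site record and also by one fixed question at the existing 3- and 6-month clinic or telephone contacts. The question should have the same wording in both arms and cover any hospital stay, stroke, systemic embolism, bleeding with transfusion, or death (from the family) at any institution. Outside events should count.

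In Statistical analysis, state that a patient without an event is censored at the last contact or record entry at which event status was known. The censoring line alone is not enough: a patient who dies elsewhere would be censored before the death, so the family contact is needed too.

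The cost is one form question at two contacts and one line on censoring, with no new visit or staff. The downside is that some outside events will rest on patient report or need a discharge summary. On 24 November 2021, 80 of 500 patients had been enrolled, so 500 − 80 = 420 were still to come. Any enrolled patient already past a contact would have to be asked at the next one, or by telephone.
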